# Rationale and design of a phase II trial of dacomitinib in advanced non-small cell lung cancer patients with uncommon epidermal growth factor receptor mutations: a prospective and single arm study (DANCE study)

**DOI:** 10.1186/s12885-022-09409-3

**Published:** 2022-03-19

**Keywords:** Non-small cell lung cancer, EGFR, Uncommon, Dacomitinib

## Abstract

**Background:**

Dacomitinib is a second-generation, irreversible epidermal growth factor receptor tyrosine kinase inhibitor (EGFR-TKI). ARCHER-1050 showed that this agent can improve progression-free survival and overall survival in advanced non-small cell lung cancer patients with sensitive EGFR mutation compared to gefitinib. However, it is unclear whether dacomitinib is effective in patients with sensitizing uncommon EGFR mutations in exon 18–21. The aim of this study is to investigate the safety and efficacy of dacomitinib in these patients.

**Methods:**

This is a single arm, prospective, open label and phase II trial. Sample size will be calculated by a minimax two-stage design method based on the following parameters: α = 0.075, 1-β = 0.9, P0 = 0.20, P1 = 0.45 and a dropout rate of 10%. A total of 30 eligible patients will be included. Patients will receive continuous oral therapy with dacomitinib (45 mg/day) until disease progression, withdrawal of consent, or unacceptable toxicity, whichever occurs first. The primary endpoint is objective response rate (ORR) per RECIST version 1.1, as assessed by investigators’ review. The second endpoint is disease control rate (DCR), PFS, OS, and safety.

**Discussion:**

We conduct a single arm, phase II study to investigate the safety and efficacy of dacomitinib in advanced NSCLC patients with sensitizing uncommon EGFR mutations. The results of the DANCE study will provide new data regarding efficacy and safety of these patients.

**Trial registration:**

NCT04504071

## Background

About 50% of Asian non-small cell lung cancer (NSCLC) patients have sensitive epidermal growth factor receptor (EGFR) mutations [1, 2]. Several prospective studies have provided robust evidence that tyrosine kinase inhibitors (TKIs) targeting EGFR mutations can not only greatly improve the prognosis of patients compared to traditional chemotherapy, but also greatly improve the quality of life, establishing a new first-line treatment for these patients [3–5]. Currently, almost 200 different EGFR mutation types have been identified. Deletion in exon 19 (19del) and point mutation in exon 21 (21L858R) are the most common, accounting for 85%-90% of the entire EGFR mutation spectrum [1, 6]. In addition to classical mutation (19del or 21L858R), uncommon EGFR mutations were also occasionally identified in clinical practice.

Several retrospective studies investigated the efficacy of first-generation EGFR-TKIs in these patients, but the results have sometimes been controversial due to the small sample size [7–9]. Osimertinib is a third-generation EGFR-TKI. FLAURA study showed that this agent is superior compared with standard first-generation EGFR-TKI in patients with 19del or 21L858R (ORR: 80% vs. 76%, OR = 1.27, 95% CI, 0.85–1.90, *P* = 0.24; PFS: 18.9 m vs. 10.2 m, HR = 0.46, 95% CI, 0.37–0.57, *P* = 0.001) [10], however, for patients with uncommon EGFR mutations, osimertinib is not that impressive. In a single arm, phase II study, 37 advanced NSCLC patients with uncommon EGFR mutation were treated with osimertinib and 61% received osimertinib as first-line treatment. ORR was 50%. Median PFS and DOR were only 8.2 months and 11.2 months, respectively. Median OS was not reached and the 18-months survival rate was 56%. Subgroup analysis showed that patients with S768I poorly response to osimertinib because the ORR was only 38%. [11]. Afatinib is a second-generation EGFR-TKI, a combined post-hoc analysis of LUX-Lung 2/3/6 showed that afatinib was active in advanced NSCLC patients that harbored certain uncommon EGFR mutations. 71.7% patients had ORR and DCR was 84.2%. Median PFS and OS were 10.7 and 19.4 months, respectively. Subgroup analysis suggested that afatinib showed clinical activity in different mutation type. The ORR in patients with G719X, L861Q and S768I were 77.8%, 56.3% and 100%; median PFS were 13.8 months, 8.2 and 14.7 months, respectively; median OS were 26.9 months, 17.1 months and not reached, respectively [12]. Based on these data, afatinib was preferred in patients with uncommon EGFR mutations.

Dacomitinib is an orally taken, irreversible small-molecule inhibitor of EGFR, HER-2 and HER-4. In ARCHER-1050 study, the median progression-free survival (PFS) was 14.7 months in the dacomitinib group, which was statistically superior compared to gefitinib (9.2 months, HR = 0.59, 95% CI 0.47–0.74; *P* < 0.0001). ORR of dacomitinib is 75% [13]. The updated results also suggested that this agent is the first second-generation EGFR-TKI that was demonstrated to improve overall survival (OS) in advanced NSCLC with 19del or 21 L858R (34.1 months vs. 26.8 months, HR = 0.76, 95% CI, 0.58–0.99, *P* = 0.044) [14]. Subgroup analysis suggested that first-line dacomitinib was associated with significant prolongation of PFS and improved OS compared with gefitinib in Asian patients [15]. Adverse event can be well managed with standard medical management and dose modifications [16]. However, it is still unclear whether this agent is effective in patients with uncommon EGFR mutations in exon 18–21. Basic research data suggested that dacomitinib may be active in lung cancer cells with sensitive uncommon EGFR mutation. In lung cancer with exon 18 mutation, the 90% inhibitory concentration of dacomitinib in transfected Ba/F3 cells were lower than the trough concentrations [17]. Case report of a 71-year-old NSCLC woman with 18 G719A showed marked regression when dacomitinib was administered [18]. Based on these results, we proposed our hypothesis that dacomitinib is active for patients with uncommon EGFR mutations.

We conduct this phase II study aiming to investigate the safety and efficacy of dacomitinib in advanced NSCLC patients with uncommon EGFR mutations.

## Methods/Design

### Study design

This is a single arm, prospective, single center, open-label, phase II trial. Eligible patients should begin continuous dacomitinib treatment 3 days after enrollment. Subjects will self-administer dacomitinib 45 mg orally once daily in 21-day cycles until disease progression, withdrawal of consent, death or unacceptable toxicity, whichever occurs first. Treatment option including immunotherapy, was at the investigators’ discretion after disease progression. Dose reductions due to grade 3 or worse treatment-related toxicity or prolonged grade 2 adverse events lasting more than one cycle were permitted. Dacomitinib is available at three dose levels, 45 mg, 30 mg, and 15 mg. Efficacy assessment will be performed every 6 weeks (± 3 days).

The primary endpoint is objective response rate (ORR) per RECIST version 1.1, as determined by investigators’ review. The second endpoint is disease control rate (DCR), PFS, OS, safety and laboratory abnormalities according to the National Cancer Institute Common Terminology Criteria for Adverse Events (CTCAE) v 4.03. Tumor tissue and peripheral blood will be collected at baseline, first assessment (blood only) and disease progression for exploratory analysis (Fig. 1). We have three exploratory endpoints: a) the relationship between ct-DNA clearance at first assessment and response depth; b) drug resistance mechanism; and c) consistency between tissue and baseline peripheral blood. The first patient has been recruited at the end of October, 2021. This study has been registered with clinicaltrial.gov, and the registration number is NCT04504071.

**Fig. 1 Fig1:**
[figure not shown]
Study schema

### Inclusion criteria

Only patients who meet all of the following criteria will be enrolled in this study:

(1) According to the 8th edition of the AJCC/UICC TNM staging system for NSCLC, patients with locally advanced (stage III B/III C), metastatic or recurrent (stage IV) NSCLC confirmed by histology or cytology who are unable to undergo surgery and radical concomitant radiochemotherapy and are confirmed to have at least one measurable lesion according to RECIST 1.1.

(2) Patients harboring uncommon EGFR mutations. Uncommon EGFR mutations were defined as mutations in exon 18–21, except for 19del, 21L858R, and well-established drug resistant types (20 insertion, T790M, L747S, L747P, D761Y, T854A). Mutations should be previously reported as sensitive to first- or second-generation TKIs. Detailed mutation types include [19–24].Mutation in exon 18: G719X(X = A/C/S/D/E), 18del, E709X(X = G/M/V/H/D/A/K), V689M, S720P/F, P699S, N700D, E709Q, G721A, V740A, L718P;Mutation in exon 19: Few exon 19-point mutations with unknown structure and kinase activity have been found in EGFR-TKI responders; however, a new class of sensitizing mutations, exon 19 insertions, were recently found, and those patients were also eligible for this study: I744_K745insKIPVAI, K745_E746insIPVAIK, K745_E746insVPVAIK, K745_E746insTPVAIK.Mutation in exon 20: Including S768I, V765A, T783A, V774A, S784P, R776C, R776H, V765M, G779C, G779F, G779S, T783A, T783I, L798F, L798H, K806E, Q812R, L814P.Mutation in exon 21: L861Q, R831H, V834I, L838P, L861R.Others: Patients with complex mutations but do not have drug-resistant patterns (e.g., 18G719A + 20S768I, 18 E709X + 21L861Q) are also eligible. However, individuals who have common mutations (e.g., 19del + 21L861Q, 18G719X + 21L858R) were not eligible.

(3) Age ≥ 18 years and ≤ 75 years;

(4) Performance status (PS) score: 0 to 2.

(5) Previously untreated with EGFR-TKIs, including first-, second- or third-generation agents. Subjects who were only treated with chemotherapy were eligible, as well as patients who have received adjuvant chemotherapy, but disease recurrence must occur at least 6 months after the last dose of chemotherapy. Palliative radiotherapy must be completed 7 days before the first dose of study drugs;

(6) The main organs function is normal, that is, the following criteria are met:Good hematopoietic function, defined as absolute neutrophil count ≥ 1.5 × 10^9^ /L, platelet count ≥ 100 × 10^9^ /L, hemoglobin ≥ 90 g/L [no blood transfusion or no erythropoietin (EPO) dependence within 7 days prior to enrollment]Biochemical test results should meet the following criteria: BIL < 1.25 times the upper limit of normal value (ULN); ALT and AST < 2.5 × ULN; in case of liver metastases, ALT and AST < 5 × ULN; Cr ≤ 1.5 × ULN or creatinine clearance (CCr) ≥ 60 ml/min; coagulation function is good, INR and PT ≤ 1.5 times ULN; if the subject is receiving anticoagulant treatment, PT should be within the prescribed range of use of anticoagulant drugs;

(7) Women of child-bearing age should agree to take contraceptive measures (such as intrauterine devices, contraceptives, or condoms) during the study and for 6 months after the study; non-breast-feeding patients whose serum or urinary pregnancy test should be negative; male patients should agree to take contraceptive measures during the study and for 6 months after the study.

(8) Patients are voluntarily enrolled into the study, sign the informed consent form and have good compliance.

### Exclusion criteria

Patients who meet any of the following criteria will be excluded:

(1) Small cell lung cancer (including mixed small cell and non-small cell lung cancer);

(2) Patients who have received EGFR-TKIs as adjuvant or salvaged treatment;

(3) Patients with 19del or 21L858R or well-established drug resistant type;

(4) Patients with many factors affecting oral medication such as dysphagia, gastrointestinal resection, chronic diarrhea, or intestinal obstruction;

(5) Patients who are known to have brain metastases, including asymptomatic metastasis, spinal cord compression, carcinomatous meningitis, or brain or leptomeningeal disease diagnosed by CT or MRI at the time of screening;

(6) Patients with severe and/or uncontrolled diseases, such as:Unstable angina pectoris, symptomatic congestive heart failure, myocardial infarction within 6 months before randomization, severe uncontrolled arrhythmias; uncontrolled blood pressure (systolic blood pressure > 140 mmHg, diastolic blood pressure > 90 mmHg);Active or uncontrolled serious infection;Liver diseases such as cirrhosis, decompensated liver disease, acute or chronic active hepatitis;Uncontrolled eye inflammation or eye infection, or any condition that may lead to the above-mentioned ocular diseases;Poorly controlled diabetes (fasting blood glucose (FBG) > 10 mmol/L);Routine urine test result indicating that urine protein ≥  +  + and 24-h urine protein quantitation is confirmed to be > 1.0 g;Active tuberculosis, etc.;Uncontrolled hypercalcemia (> 1.5 mmol/L calcium ion or calcium > 12 mg/dL or corrected serum calcium > ULN), or symptomatic hypercalcemia requiring continued diphosphate therapy;Long-term unhealed wounds or fractures;

(7) Patients who have a history of psychotropic drug abuse and cannot abstain from it or have mental disorders;

(8) Patients who are known to have severe allergies (≥ grade 3) to active ingredients and any excipients of dacomitinib;

(9) Patients who have other malignant tumors (except radical cervical carcinoma in situ, non-melanoma skin cancer, etc.) at the same time; patients who are evaluated by the investigator to have concomitant diseases that seriously endanger the safety of the patients or affect the patients’ completing the study;

(10) The subjects or their sexual partners cannot or refuse to take effective contraceptive measures during the clinical trial;

(11) Pregnant or breast-feeding women;

(12) Patients in other situations who are evaluated by the investigator to be ineligible to be enrolled.

### Rationale for setting the number of enrolled participants

Sample size will be calculated by a minimax two-stage design method based on the following parameters: α = 0.075, 1-β = 0.9, P0 = 0.20, P1 = 0.45. The optimal two-stage design tests the null hypothesis that *P* ≤ 0.20 versus the alternative that *P* ≥ 0.45. After testing the drug on 12 patients in the first stage, the trial will be terminated if 2 or fewer patients respond. If the trial goes on to the second stage, a total of 27 patients will be studied. If the total number responding is less than or equal to 8, the drug is considered noneffective. Assuming a dropout rate of 10%, 30 patients will be finally enrolled.

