### Statistical methods

Best overall response will be summarized for the FAS population based on the investigator’s assessment. The number and percent of subjects achieving objective responses (CR or PR) will be summarized along with corresponding 2-sided 95% CI using binomial distribution. Median progression-free survival (PFS) and overall survival (OS) will be calculated based on the Kaplan–Meier method. Baseline characteristics, incidence, and severity of adverse events will be summarized.

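### The final boundary of 8 responders holds for 27 patients, but 30 are enrolled and nothing says which 27 the rule uses; applied to 28–30 evaluable patients it would exceed the stated alpha of 0.075

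*Protocol article*

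**What the plan says.** All design figures are in the Protocol article, in the section on the rationale for the number of participants.

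- Parameters: "α = 0.075, 1-β = 0.9, P0 = 0.20, P1 = 0.45". The design "tests the null hypothesis that *P* ≤ 0.20 versus the alternative that *P* ≥ 0.45", so the test is one-sided.
- Stage 1: "After testing the drug on 12 patients in the first stage, the trial will be terminated if 2 or fewer patients respond".
- Stage 2: "If the trial goes on to the second stage, a total of 27 patients will be studied".
- Final rule: "If the total number responding is less than or equal to 8, the drug is considered noneffective".
- Enrolment: "Assuming a dropout rate of 10%, 30 patients will be finally enrolled". The abstract repeats the figure: "A total of 30 eligible patients will be included".

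Under Statistical methods, "Best overall response will be summarized for the FAS population", with a two-sided 95% confidence interval for the response rate. The FAS section starts from everyone enrolled and removes three groups: those without consent or who retract it, those never given protocol treatment, and those with no data at all after enrolment. A patient who takes dacomitinib and is lost before the first scan, but has some post-enrolment data, stays in.

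**The concern.** The rule is a count of responders, and such a count has the stated error rates only for the number of patients it was derived for. Three numbers are in play: 27 for the rule, 30 for enrolment, and a FAS that may be anything up to 30. The article does not connect them. It does not say whether the rule is read on the FAS, on evaluable patients or on the first 27, and it gives no boundary for 28, 29 or 30.

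The 10% allowance does not settle this, because the assumed dropout is not tied to the FAS exclusions. If fewer than three patients are lost, more than 27 have a chance to respond, and reaching nine responders becomes easier when the true rate is only 0.20. Nine responders is 33.3% of 27 but 30.0% of 30. This is the only stated rule for calling the drug effective or not, so an ambiguity here can change the trial's conclusion.

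**Working it through.** **Inputs.** From the sample size section: n1 = 12, r1 = 2, n = 27, r = 8, P0 = 0.20, P1 = 0.45, alpha 0.075, power 0.90, dropout 10%.

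**Formula.** The probability of declaring the drug effective at true response rate p is

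P(p) = Σ over x from r1+1 to n1 of Bin(x; n1, p) × Pr[Y ≥ r + 1 − x], with Y ~ Bin(n − n1, p).

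At p = 0.20 this is the type I error; at p = 0.45 it is the power.

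**1. The plan's own design.** With (r1/n1, r/n) = (2/12, 8/27), P(0.20) = 0.0676 and P(0.45) = 0.9014. Both targets are met. A search over all two-stage designs up to n = 36 returns this design as both minimax and optimal. The inflation is also right: 27 / (1 − 0.10) = 30.

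**2. More evaluable patients.** Stage 1 stays at 2/12 and each patient can respond with probability p.

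| Evaluable n | Boundary 8: alpha | Boundary 8: power | Boundary 9: alpha | Boundary 9: power |
|---|---|---|---|---|
| 27 | 0.0676 | 0.901 | – | – |
| 28 | 0.0809 | 0.917 | 0.0368 | 0.864 |
| 29 | 0.0953 | 0.929 | 0.0456 | 0.888 |
| 30 | 0.1105 | 0.938 | 0.0555 | 0.907 |

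With the boundary left at 8, every total above 27 breaks the 0.075 limit.

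**3. How likely is a total above 27?** The article assumes 10% dropout. Taking losses as independent (my assumption), the chance that at least 28 of 30 remain is Pr[Bin(30, 0.9) ≥ 28] = 0.228 + 0.141 + 0.042 = 0.41. If the 12 stage-1 patients are all evaluable and each of the 18 later ones is evaluable with probability 0.9, the average type I error with boundary 8 is 0.085.

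**4. Dropouts kept in as non-responders.** A patient who cannot respond adds nothing to a count. With 27 evaluable patients and three such dropouts after stage 1, the FAS is 30 but the error rates are exactly those of step 1: 0.0676 and 0.9014. If instead 10% of all 30, stage 1 included, cannot respond and are not replaced, the effective rates are 0.9 × 0.20 = 0.18 and 0.9 × 0.45 = 0.405. Boundary 8 then gives alpha 0.065 and power 0.868.

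**5. What boundary 9 costs.** At 30 patients it gives 0.0555 and 0.907 only if all 30 can respond. If three of the 30 are post-stage-1 dropouts counted as non-responders, the calculation is (2/12, 9/27) and power is 0.834. With the thinned rates of step 4 it is 0.806.

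**The case against.** The strongest reply is that the rule is stated for 27 patients and for no other number. The text gives 27 as the total studied, and 30 appears only as an allowance for loss. The Statistical methods section uses the FAS to summarise response with a confidence interval; it does not mention the decision rule. Read that way, with exactly the planned loss, both targets are met. Which patients enter the rule may also be set out in the full protocol or SAP, which are not shown.

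Most of this stands. A reader might infer that the plan exceeds its stated alpha, or that its arithmetic is wrong. The documents support neither: the excess needs more than 27 patients able to respond and the boundary of 8 applied to all of them, and the figure of 0.110 needs no loss at all.

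A reader might also infer that the 10% inflation fails because retained dropouts dilute the response rate. That does not follow for a count rule, as step 4 shows. The power of 0.868 comes from unreplaced losses within the first 12, which the article does not address. Nor can both harms be charged to the same patients: extra patients raise alpha only if they can respond.

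What does not stand is that nothing needs saying. The article prints the boundary, the 27, the 30 and the FAS definition, and as printed they leave open which patients are counted. That is a rule fixed incompletely, not merely a detail left out. The confidence interval does not fill the gap: even 9/27 has an exact 95% interval of 0.165 to 0.540, which includes 0.20, although nine responders passes the rule.

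**Conclusion.** The point holds in a conditional form. The 2/12 and 8/27 design is correct (alpha 0.0676, power 0.9014). The article does not link it to the 30 enrolled patients or to a FAS that can hold 28 to 30. If fewer than three patients are lost and the boundary of 8 is read on the whole FAS, the type I error would be 0.081, 0.095 or 0.110 instead of at most 0.075.

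These figures assume that stage 1 stays at 2/12, that the extra patients join in stage 2, and that each can respond with probability 0.20 under the null hypothesis. Dropouts counted as non-responders do not themselves raise alpha. At the planned 10% loss, a total above 27 is a realistic outcome (about 0.41 under independent losses).

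**What to change.** **Preferred.** State, before the final count is known, that the 2/12 and 8/27 rule is applied to the first 12 and the first 27 evaluable FAS patients in enrolment order, with evaluable defined in advance. Add that the response rate and confidence interval in the full FAS are descriptive. This keeps alpha at 0.0676 and power at 0.9014 whenever at least 27 evaluable patients are reached. It costs one sentence and no patients; up to three enrolled patients would not count towards the formal decision.

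**Alternative.** Give a boundary for each attained number of evaluable patients: 8 at 27, and 9 at 28, 29 or 30. Alpha is then at most 0.0676. The cost should be stated: power is 0.864 at 28, 0.888 at 29 and 0.907 at 30. It is lower if non-evaluable patients are counted in n as non-responders: 0.834 with boundary 9 and three post-stage-1 dropouts among 30. The attained number must therefore count evaluable patients, not everyone in the FAS.

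If the full protocol or SAP already contains either statement, the article needs only to repeat it.

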### Population to be analyzed

Efficacy will be analyzed based on full analysis set (FAS) and per-protocol set (PPS). Safety will be analyzed based on safety analysis set (SAS).

#### FAS

All the participants enrolled in this study except: (I) patients without informed consent or who retract their informed consent; (II) patients who do not receive any protocol treatment; and (III) patients who don’t have any data after enrollment. Final decisions will be made after discussion with the trial statistician and principal investigator.

#### PPS

All the participants in the FAS except patients with violation of inclusion/exclusion criteria or violation for prohibited concomitant drugs/therapies.

#### SAS

Patients who received at least 1 dose of dacomitinib.

### Statistical methods

Best overall response will be summarized for the FAS population based on the investigator’s assessment. The number and percent of subjects achieving objective responses (CR or PR) will be summarized along with corresponding 2-sided 95% CI using binomial distribution. Median progression-free survival (PFS) and overall survival (OS) will be calculated based on the Kaplan–Meier method. Baseline characteristics, incidence, and severity of adverse events will be summarized.

